## Abstract

**Background:**

Coordinated Specialty Care (CSC) programs provide evidence-based services for young people with a recent onset of a psychotic disorder. OnTrackNY is a nationally recognized model of CSC treatment in New York state. In 2019, OnTrackNY was awarded a hub within the Early Psychosis Intervention Network (EPINET) to advance its learning health care system (LHS). The OnTrackNY network is comprised of 23 CSC teams across New York state. OnTrack Central, an intermediary organization, provides training and implementation support to OnTrackNY teams. OnTrack Central coordinates a centralized data collection protocol for quality improvement and evaluation of program fidelity and a mechanism to support practice based-research. OnTrackNY sites’ breadth coupled with OnTrack Central oversight provides an opportunity to examine the impacts of the COVID-19 crisis in New York State, and supplementary funding was awarded to the OnTrackNY EPINET hub in 2021 for that purpose.

**Methods:**

This project will examine the implications of modifications to service delivery within the OnTrackNY LHS during and after the COVID-19 crisis. We will use the Framework for Reporting Adaptations and Modification-Enhanced (FRAME) to classify systematically, code, and analyze modifications to CSC services and ascertain their impact. We will utilize integrative mixed methods. Qualitative interviews with multi-level stakeholders (program participants, families, providers, team leaders, agency leaders, trainers (OnTrack Central), and decision-makers at the state and local levels) will be used to understand the process of making decisions, information about modifications to CSC services, and their impact. Analysis of OnTrackNY program data will facilitate examining trends in team staffing and functioning, and participant service utilization and outcomes. Study findings will be summarized in a *CSC Model Adaptation Guide*, which will identify modifications as fidelity consistent or not, and their impact on service utilization and care outcomes.

**Discussion:**

A *CSC Model Adaptation Guide* will inform CSC programs, and the state and local mental health authorities to which they are accountable, regarding modifications to CSC services and the impact of these changes on care process, and participant service utilization and outcomes. The guide will also inform the development of tailored technical assistance that CSC programs may need within OnTrackNY, the EPINET network, and CSC programs nationally.

**Trial registration:**

NCT04021719, July 16th, 2019.

Contributions to the literature
With the advent of the COVID-19 pandemic, Coordinated Specialty Care (CSC) teams made modifications to how they provided services; however, the impact of these changes on program participants is unknown.Challenges in delivering CSC were related to shifting services to primarily using telehealth with little experience or guidance, workforce redeployment to medical units, and the inability to provide community-based interventions.An implementation science framework is used to evaluate modifications to CSC services, which will help determine if modifications were fidelity consistent or not and identifying those associated with positive participant outcomes.

## Background

Coordinated Specialty Care (CSC) programs provide evidence-based services for young people with recent onset of a psychotic disorder [1]. New York State’s program, OnTrackNY (OTNY), is a nationally recognized model of CSC treatment [2]. The program is implemented by a multidisciplinary team with specialized training, which provides coordinated, evidence-based treatments based on the interests, needs, and preferences of each participant. The program emphasizes assertive outreach and engagement and is offered for an average of 2 years. OnTrackNY teams offer participants a range of evidence-based treatment options, including individual therapy based on cognitive behavioral therapy for psychosis (CBTp), psychiatric medications, family education and support, peer support, supported education and employment, case management and community support, and a focus on physical wellness and primary care coordination. Teams focus on helping participants attain individual goals typically related to school, work, and relationships [3]. OnTrackNY has demonstrated improvements in symptoms, functioning, hospitalization, and work/school participation [4]. Guided by the Reach, Effectiveness, Adoption, Implementation and Maintenance (RE-AIM framework), OnTrackNY program implementation has been previously described [5, 6].

OnTrack Central is an intermediary organization [7, 8] responsible for training and implementation support of OnTrackNY programs. It has created systems for multi-level stakeholder engagement, a centralized data collection protocol for quality improvement and evaluation of program fidelity, and a mechanism to support practice based-research. Initial training provided to OnTrackNY teams includes a multi-day in-person introductory training in the principles and practices of the CSC model, followed by remote consultation, and training in data collection forms, procedures, and the data collection platform. Regular, on-going training is also provided for team members, based on their specialty, through frequent individual, collaborative, role and team-based phone calls, monthly care consultation calls, webinars, and use of data and fidelity reports to highlight strengths and identify areas for improvement [3].

In 2019, OnTrackNY was awarded a hub within the Early Psychosis Intervention Network (EPINET) to advance a learning health care system (LHS) through enhanced stakeholder participation and improved data infrastructure [9]. Soon after this time, the rapid rise of COVID-19 created shocks to the health care system, producing numerous rapid changes in behavioral health service delivery, in the absence of guidance from evidence or experience. It is unclear how these changes will impact the ongoing delivery of CSC services and participant outcomes. The breadth of OnTrackNY sites coupled with OnTrack Central oversight provides a unique opportunity to examine the impacts of the COVID-19 crisis in New York state. The diversity of the 23 OnTrackNY teams located throughout the state enables examination of settings with a high and low prevalence of COVID-19 infections, and diverse regulatory and workforce environments. The OnTrackNY network includes programs that operate within variable settings and communities (outpatient clinics at community agencies, state-operated facilities, and community and academic hospitals in urban, suburban, and rural areas) with very diverse participant populations.

OnTrack Central’s early engagement of the OnTrackNY network has revealed how changes due to COVID-19 have dramatically impacted CSC services. Changes in staffing due to redeployment to medical units, childcare challenges, illness, and agency requirements to provide telehealth services from on-site locations have disrupted team functioning and clinical care. The rapid shift to telehealth without the benefit of planning, technology infrastructure, or training changed service delivery overnight. Telehealth may be challenging to implement in CSC due to common challenges young people with psychosis face including structural barriers (e.g., lack of equipment, WIFI, lack of privacy), cognitive deficits, symptoms of psychosis, and elevated suicide risk. However, staff innovation and creativity could transform these challenges into improvements and advantages. Teams have had to quickly adapt to online education, employment, and community systems to help participants adjust to changes required due to COVID-19 like physical distancing and interruption to school and work. Clinicians have had to develop strategies to assess and manage suicide risk via telehealth.

In 2021, the OnTrackNY EPINET hub was awarded a COVID-19 supplement to explore the impact of the COVID-19 on OnTrack NY participants and teams, the focus of this study protocol. This study protocol uses an integrative mixed-method approach to examine the implications of modifications to service delivery within the OnTrackNY LHS during and after the COVID-19 crisis. We will use the implementation science framework, Framework for Reporting Adaptations and Modifications-Enhanced (FRAME), to systematically evaluate modifications and ascertain their impact on CSC program implementation and participant outcomes. The FRAME captures processes for modification, including reasons for the modification, what was modified, level of modification, and timing across phases of treatment [10]. The FRAME’s detailed coding system will elucidate if modifications are fidelity-consistent with the CSC model and enhance service delivery, and whether any changes are associated with reduced effectiveness [11].

## Methods/design

### Conceptual framework

The FRAME uses a detailed coding system to capture modifications, including reasons for the modification, what was modified, level of modification, and timing across phases of treatment [10]. Our focus in accord with implementation and dissemination principles [12, 13] will be on multiple methods, multiple contextual levels and stakeholders, and pragmatic assessment strategies [13]. The FRAME will guide our mixed-method assessment to capture modifications to the delivery of CSC services and whether these are fidelity-consistent [11]. The perspectives of stakeholders on the acceptability, feasibility, and perceived impact of these CSC modifications will also be examined.

### Aims

This project aims to assess:
Implications of governmental and agency-level policy changes and decision-making that shifted the delivery of behavioral health services and how these decisions impact OnTrackNY team staffing and functioning.Implications for implementation of CSC service delivery, including assessment of needed modifications by service component within the CSC model (e.g., medication management, psychotherapy, peer services, and supported employment and education services) and the phase of treatment from outreach/enrollment to discharge.Impact on participant-level care processes (e.g., utilization of services) and outcomes (e.g., symptoms, social functioning, work/school participation, use of telehealth services, satisfaction with services) overall and within participant subgroups defined by COVID-19 impact (e.g., program modifications/adaptations, high or low intensity COVID-19 penetration) and other participant risk factors and characteristics (e.g., racial/ethnic disparities, suicide risk).

### Study design

We will utilize integrative mixed methods [14]. Qualitative interviews with multi-level stakeholders (program participants, families, providers, team leaders, agency leaders, and decision-makers at the state and local levels) will help us learn about the process that various stakeholders used to determine policy changes, modifications to the implementation of CSC services, and their impact. Analysis of OnTrackNY program data will facilitate examining trends in team staffing and functioning, participant service utilization and care outcomes. We will accomplish study aims over three time periods, as indicated below (Table 1). Mapped to the dimensions of the RE-AIM framework, Table 2 provides examples of areas to be studied and influenced by input from the integrative mixed-methods from Aims 1 and 2.

**Table 1 Tab1:** Study aims, methods, and stakeholder groups

Study aims	Purpose	Methods	Stakeholder groups
Aims 1 & 2	Exploration	Interviews	OnTrackNY providers and team leaders; Agency leadership; OnTrack Central trainers; State and local-level decision makers
		Focus groups	OnTrackNY Youth, Family Advisory and Provider Councils
Aim 2	Confirmation Elaboration	Data collection Survey Fidelity review Focus groups	Participant self-report; Participant-level data collection (OnTrackNY primary clinician); Program-level data collection (OnTrackNY team leaders) Family survey OnTrackNY fidelity committee OnTrack Central leadership, OnTrackNY Youth and Young Adult Leadership, Family Advisory and Provider Councils
Aims 1–3	Exploration, Confirmation, Elaboration	Tracking Sheet	OnTrack Central technical assistance calls
Aims 2 & 3	Examination	Data analysis	OnTrackNY clinicians and participants

**Table 2 Tab2:** Data analyses examining the impact on care processes and outcomes (pre versus post-March 2020)

RE-AIM dimension	Example areas to be studied	Outcome (implementation or participant level)	Key features and subgroups associated with outcomes	Data sources
Reach	Changes in the population served	*Implementation:* Program level rates of enrollment and discharge across OTNY	Geographic areas with high and low COVID penetration.	Clinician-reported data aggregated to the program level
Effectiveness		*Participant level:* Participant characteristics at enrollment to OTNY	Referral source (e.g., inpatient unit), duration of untreated psychosis (DUP), symptoms, additional variables as identified in Aims 1 and 2	Clinician-reported data and participant self-report data
Effectiveness		*Participant level:* Participant features at time of discharge/disengagement from OTNY	Length of stay in OnTrackNY; symptoms, occupational and social functioning; use of telehealth services; satisfaction with services; other factors as identified in Aims 1 and 2	Clinician-reported data and participant self-report data
Effectiveness	Changes in participant outcomes	*Participant level:* Symptoms, social and occupational functioning, work/school participation, suicidality, and other factors identified in Aims 1 and 2	Clinical characteristics at enrollment, age, gender, race/ethnicity, DUP, educational attainment, program site, presence of identified modifications, other factors as identified in Aims 1 & 2	Clinician and participant self-reported data
Implementation	Changes in how and which services are implemented	*Implementation level:* Frequency of utilization of OTNY services overall and with particular team members (e.g., peer support, supported employment and education services)	Presence of identified modifications in a clinic (e.g., telehealth interventions), programs where staffing was affected (e.g., FTE per team), participant utilization of modifications, fidelity to the CSC model, other factors identified in Aims 1 & 2	Program-level data and clinician-reported data

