Descriptive analyses of surveys will be conducted by stakeholder group and will explore differences in use, acceptability, feasibility, and perceived impact by different OnTrackNY dimensions (location, type of program, respondent characteristics including demographics, age, time in the program). The list of major modifications from the surveys will be reviewed alongside a list of modifications generated by the ongoing, real-time tracking of modifications. In the case of divergence in type and characteristics of existing modifications or emerging modifications, the coders and study team will reconcile and revise the list of the major modifications. Modifications that meet threshold criteria (at least 50% of all stakeholder groups identified) will be considered tier 1 modifications and used in subsequent quantitative analyses examining effects on participant-level care processes and outcomes in Aim 3 work. Modifications that do not meet these threshold criteria (tier 2 modifications) will be summarized and described based on OnTrackNY dimensions by level of operational salience.

#### Aim 3

As in prior work with OnTrackNY longitudinal data [4, 21, 22], we will utilize generalized linear mixed models which account for the natural multi-level structure of the data of repeated measures on participants (every 90 days by providers and 6-month participant self-report) nested within teams. Importantly, we will incorporate a fixed time period indicator of the pre-March 2020 period allowing for a categorical indicator for each calendar month post-March 2020 until the end of the study period (likely first quarter of 2022). Outcomes and predictors will vary depending on the question (Table 2). Still, in all cases, we will use best statistical modeling practices for estimating and testing effects (focusing on effect sizes and uncertainty using 95% confidence intervals).

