#### Statistical power

With over 2200 participants served to date, 23 different teams across the state, over 500 new enrollees in 2019, and the program continually growing, we have adequate power to address questions of change. For example, for questions regarding the population served, we have 80% power to detect a shift in early discharge of participants (i.e., disengagement before 1 year, historically at ~25%) [23], as small as 7%. Power is similar for detecting changes in participant outcomes, e.g., percent of participants in work or education consistently for the whole year in the pre period as compared to post March 2020. For assessing associations between team level characteristics (e.g., modifications) and frequency of participants receiving services, we have 80% power to detect at least medium effect sizes (Cohen’s d=0.40) assuming intraclass correlation (ICC=0.10) historically found for OTNY outcomes within teams. Finally, the diversity of the participants and teams across the state provide adequate power to examine racial minority subgroups and geographic areas with high and low COVID penetration (New York City vs. upstate areas).

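### Comparing length of stay and other features among discharged participants before and after March 2020 shows a change even when leaving rates have not changed

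*Protocol article*

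**What the plan says.** Table 2 (Study design) is titled as a set of analyses comparing the periods before and after March 2020. One Effectiveness row gives as its outcome "Participant features at time of discharge/disengagement from OTNY". The column of key features and subgroups in that row lists length of stay first, then symptoms, functioning, telehealth use and satisfaction.

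Under Statistical methods, Aim 3, the stated model class is: "we will utilize generalized linear mixed models which account for the natural multi-level structure of the data". The repeated records come every 90 days from providers and every 6 months from participants. The model has one indicator for the pre-March 2020 period and one category per calendar month afterwards, "until the end of the study period (likely first quarter of 2022").

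Statistical power describes early discharge as "disengagement before 1 year, historically at ~25" per cent, and claims 80% power for a shift as small as 7%. The Background says that the programme is offered for an average of 2 years. The Aim 3 data section places the pre period from October 2013 to March 2020.

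**The concern.** Discharge happens once, at a time that varies between people. A comparison of features at discharge takes in only those whose discharge has been observed, and who they are depends on how long each period can watch people.

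- **Classed by discharge date.** The early years of a new, growing programme contain many short stays, because few people have been enrolled long enough to finish. Later years contain more completed courses. Stays appear to lengthen.
- **Classed by enrolment date.** No one enrolled after March 2020 can show a stay longer than about 22 to 24 months, and most can show far less. Stays appear to collapse and nearly all discharges look early.

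The sign of the false change thus depends on which date assigns the period. Symptoms and functioning at discharge are affected too, in so far as they vary with time in care. The findings feed the Adaptation Guide, where either artefact could be read as an effect of telehealth or other service changes.

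**Working it through.** **Inputs from the article:** 25% early discharge by 1 year; target shift of 7 points; more than 2200 served and more than 500 enrolled in 2019; pre period October 2013 to March 2020 (78 months); end in the first quarter of 2022 (taken as 22 to 24 months after March 2020); care averaging 2 years. **Assumed:** two-sided 5% test, enrolment growing linearly to 500 a year and then flat, constant hazard of leaving unless stated, and the group sizes below.

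**1. The plan's own figure.** Take 1700 pre enrollees (2200 less the 500 of 2019) and 417 post enrollees with a full year of follow-up (500 × 10/12, for a 22-month end). Compare 25% with 32%, ignoring clustering.
- Pooled proportion = (1700 × 0.25 + 417 × 0.32)/2117 = 0.264.
- Null SE = √[0.264 × 0.736 × (1/1700 + 1/417)] = 0.0241.
- Alternative SE = √[0.1875/1700 + 0.2176/417] = 0.0251.
- z = (0.07 − 1.96 × 0.0241)/0.0251 ≈ 0.91, so power is 0.82.

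The stated 7 points is reproduced, and by a cohort with complete 12-month follow-up.

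**2. Discharged participants only, no true change (simulation).** Disengagement hazard λ = −ln(0.75) = 0.288 per year, and planned discharge at about 2 years.

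| Period assigned by | Early share, pre vs post | Mean stay, pre vs post |
|---|---|---|
| Discharge date | 36% vs 27–28% | 1.32–1.34 vs 1.46–1.48 years |
| Enrolment date | 25–26% vs about 68–83% | about 1.5 vs 0.56–0.76 years |

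The ranges reflect the end month and the spread of planned discharge. A different stay distribution, with an overall mean of 24 months, gives by discharge date 40% vs 30% and 15.3 vs 19.4 months. Capping those stays at 30 months gives 37% vs 27% and 15.8 vs 18.2 months. In the same distributions, 65–70% of observed discharges among post enrollees are early.

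**3. The 1-year binary, if everyone still enrolled were counted as retained.** With even enrolment, 12/24 = 50% to 12/22 = 55% of post enrollees have under 12 months of follow-up. Their expected observed risk is 1 − 0.25/0.288 = 13.1%.
- 24-month end: (12 × 25% + 12 × 13.1%)/24 = 19.0%, a shift of −6.0 points.
- 22-month end: (10 × 25% + 12 × 13.1%)/22 = 18.5%, a shift of −6.5 points.
- Front-loaded to back-loaded leaving: −4.7 to −8.5 points.
- Pre enrollees also cut at March 2020: pre rate = (1700 × 25% + 500 × 13.1%)/2200 = 22.3%, a net shift of −3.2 to −3.8 points.
- Full 12-month window in both periods: 0.

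**4. Stays that cross March 2020.** Classed by enrolment date with no true change, the shift is 0. With a true rise to 32%, the 500 who cross have a risk of 28.6%. The pre rate becomes (1700 × 25% + 500 × 28.6%)/2200 = 25.8%, and the observed rise is 6.2 points instead of 7.

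**5. The alternative.** In the simulation of step 2, events and person-time in the first year of care were split at March 2020 and censored at the data cut. The 1-year risk came back as 25% vs 25%.

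**The case against.** The strongest reply is that this is a condensed article. Table 2 offers examples, length of stay is in the features column instead of the outcome column, the end date is only likely, and good modelling practice is promised. Denominators and censoring rules commonly sit in a fuller plan. Much of this stands, and it rules out several stronger readings that a reader might infer:

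- **That the plan counts people with short follow-up as not discharged early.** No sentence says so. Step 3 is conditional, and a full 12-month window removes the bias.
- **That the 7-point power claim fails.** Step 1 shows that it is compatible with a complete 12-month cohort.
- **That stays crossing March 2020 create a false shift.** With classing by enrolment date they only dilute a real one.
- **That a generalized linear mixed model cannot handle censoring.** A discrete-time hazard model with a team random effect is itself a binomial mixed model on person-period records, and monthly calendar indicators suit it.
- **That early discharge is the only outcome with stated power.** The same section also gives power for team-level associations and for work or education.

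The reply does not rescue the discharge row. Conditioning on discharge and splitting at March 2020 are both the table's own framing. A 12-month window repairs the 1-year binary, but not length of stay or other features among the discharged.

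**Conclusion.** The concern holds for the at-discharge comparison. Followed as framed in Table 2, it shows a difference where none exists, whichever date assigns the period. By discharge date the difference is about 0.15 years in mean stay and 8 to 10 points in the early share of discharges. By enrolment date it is several times larger and points the other way. These sizes rest on the assumed hazard, growth and stay distribution. The direction follows from a short post period and a programme that grew from nothing in 2013.

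For the 1-year binary, the article leaves the denominator open. The possible artefact runs from 0 (full window) through 3 to 4 points (both periods cut alike) to about 6 points (only post enrollees cut), set against a 7-point target. That calls for a stated rule and does not show an error in the power claim.

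**What to change.** Analyse discharge or disengagement in all enrollees, not only those discharged:

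- Fit a discrete-time hazard model, that is, a binomial mixed model on the 90-day records with a team random effect.
- Enter calendar period as a time-varying covariate, so that a stay crossing March 2020 contributes to both periods.
- Censor at the data cut, and treat planned completion as a competing event.
- Report 1-year cumulative incidence of disengagement, and restricted mean time in care over a horizon that both periods cover, in place of length of stay among the discharged.
- If a simple 1-year percentage is also shown, limit it to people enrolled at least 12 months before the cut, and state which date assigns the period.

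The cost is wording and slightly more analysis work. Length of stay is already to be derived, so enrolment and discharge timing must be held. The model class is unchanged, and no later data cut is needed.

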## Discussion

The rapid rise of COVID-19 created shocks to the health care system. To combat the rapid rise of infections, the New York State (NYS) stay at home order (effective March 22, 2020) required all non-essential businesses to cease in-person operations, required people to shelter in place, and move to distance technology [16]. Engagement with the OnTrackNY network revealed how these conditions have dramatically impacted CSC services. For example, many sites rapidly moved from providing 0% to nearly 100% telehealth with no time to plan, and with limited infrastructure, experience, or training. Agencies faced redeployment of staff to medical units, staff members’ childcare challenges, and illness of team members as well as agency requirements regarding the need to be on-site, which caused staff changes and disruptions. Some participants faced access barriers (limited availability of cell phones, WIFI). Moreover, telehealth may be particularly challenging in CSC treatment, with participants experiencing cognitive deficits and symptoms of psychosis [23], as well as a suicide risk. Despite these challenges, OnTrack Central has begun to learn about staff innovation and creativity that could transform these challenges to improvements and advantages. OnTrackNY teams remain committed to their mission to provide high-quality care to improve participants’ outcomes.

This crisis provides an opportunity to examine how CSC teams, facing a substantial and unexpected disruption, can respond and adapt to the changing needs of participants, families, and their own agencies, to maintain high-quality services. The health care and economic effects of the COVID-19 crisis are likely to persist for some time. Some changes in health care delivery, particularly increased use of telehealth may be permanent. It is crucial to understand the impact of these changes on service delivery and on participant outcomes [24]. This is a unique opportunity to understand how decisions to adapt service delivery are made, how they are implemented in response to the crisis, and how they impact different stakeholder groups, including policy leaders, providers, participants, and family members. This study, supported by supplementary COVID-19 funding (2021–2023), provides a unique opportunity to examining this system transformation by systematically capturing service modifications using implementation science frameworks (RE-AIM and FRAME) and dynamically examining this process as it unfolds.

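### A pre/post March 2020 change in clinician-recorded suicidality or symptoms mixes true change with changed detection, in an unknown direction, and the stated model cannot separate them

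*Protocol article*

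**What the plan says.** Table 2 (Study design) is headed as a comparison of the periods before and after March 2020. Its row on changes in participant outcomes lists "Symptoms, social and occupational functioning, work/school participation, suicidality, and other factors identified in Aims 1 and 2", and gives the data source as "Clinician and participant self-reported data". It does not say which source carries which outcome. Under Statistical methods, Aim 3, the reporting schedule is "every 90 days by providers and 6-month participant self-report". The mixed model there has one indicator for the whole pre-March 2020 period and one for each calendar month afterwards.

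On how contact changed, the Discussion dates the stay at home order to March 22, 2020 and says "many sites rapidly moved from providing 0% to nearly 100% telehealth with no time to plan". The Background adds: "Clinicians have had to develop strategies to assess and manage suicide risk via telehealth". It also lists missing equipment, lack of privacy, symptoms and elevated suicide risk as difficulties for telehealth in this population.

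The Aim 3 (examination) section treats the crisis as a natural experiment for participant outcomes, and the Adaptation Guide is to carry findings linked to favourable outcomes. The limitations in the Discussion name recall bias but no change in how outcomes are ascertained.

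**The concern.** The date that defines the comparison is also the date on which, at many sites, clinicians began to observe participants in a different way. What a clinician records about suicidality depends on whether it is present and on whether the contact brings it out. If the second factor shifts in March 2020, the pre/post contrast in clinician-recorded suicidality no longer estimates change in suicidality alone. The same holds for clinician-rated symptoms.

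The problem reaches past the calendar contrast. The same row of Table 2 uses the presence of identified modifications as a feature associated with outcomes. Telehealth is the article's own example of a major modification. For that modification, the exposure and the mode of measurement are largely the same variable.

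At stake is what the study may conclude about one of the most serious outcomes it names. If telehealth detected less, a recorded fall could be spurious or a true rise could be hidden. If it detected more, a recorded rise could be an artefact of better detection.

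**Working it through.** The article states no figure on this point, so there is nothing to reproduce. The check has two parts.

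**1. What the stated model can identify**

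- Quantity estimated: the change in the recorded outcome from the pre-period to each later month.
- Recorded rate = true rate × probability of detection (false positives ignored).
- Post/pre ratio of recorded rates = (ratio of true rates) × R, where R = detection after March 2020 ÷ detection before.
- The period and month indicators estimate only the product. No term in the described model carries R, and the article describes no record of the contact mode behind each rating.

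**2. Size, under assumptions**

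The article gives neither a suicidality rate nor a detection rate. Assumed: a pre-period recorded rate of 10%, 15% or 25%; R from 0.7 to 1.2; no true change. For sample size, the article gives over 2200 people served and over 500 new enrollees in 2019. I use 500 post and 2200 − 500 = 1700 pre, independent observations, no clustering, two-sided alpha 0.05.

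Recorded post rate = pre rate × R. True relative rise recorded as no change = 1/R − 1.

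| R | 10% becomes | 15% becomes | 25% becomes | True rise recorded as no change |
|---|---|---|---|---|
| 0.7 | 7.0% | 10.5% | 17.5% | 43% |
| 0.8 | 8.0% | 12.0% | 20.0% | 25% |
| 0.9 | 9.0% | 13.5% | 22.5% | 11% |
| 1.0 | 10.0% | 15.0% | 25.0% | none |
| 1.2 | 12.0% | 18.0% | 30.0% | none; a true fall of 1 − 1/1.2 = 17% is recorded as no change |

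Chance of a significant but spurious change: Φ[(|p1 − p2| − 1.96 × SE0)/SE1], with SE0 the pooled and SE1 the unpooled standard error.

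- p1 = 0.15, R = 0.8, p2 = 0.12: SE0 = 0.01782, SE1 = 0.01692. (0.03 − 1.96 × 0.01782)/0.01692 = −0.29, so Φ = 0.39 for a false fall.
- p1 = 0.15, R = 1.2, p2 = 0.18: SE0 = 0.01850, SE1 = 0.01924. (0.03 − 1.96 × 0.01850)/0.01924 = −0.33, so Φ = 0.37 for a false rise.
- For base rates of 10%, 15% and 25%, R = 0.8 gives a false fall in about 26%, 39% and 64% of studies. R = 0.7 gives 53%, 74% and 95%. R = 1.0 gives the nominal 2.5% in each direction.

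The bias in the ratio is R whatever the base rate. A larger sample narrows the interval around the biased value and does not remove the bias.

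**The case against.** The strongest case against the point is that no detection loss is documented. The Background says clinicians had to develop new strategies, which describes new practice and not poorer practice, and the article expects that staff innovation may turn some difficulties into advantages. This stands. A reader might infer that telehealth under-detected suicidality, so that the plan would show improvement and conceal harm. The documents do not support that reading, because they give no detection rate in either mode.

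Three further objections stand in part.

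- **Sources.** Self-report is listed beside clinician report, on its own schedule, and nothing says the two will be pooled. A reader should not infer pooling. But the article does not say which source carries suicidality, and it does not describe using one to check the other.
- **Data already planned.** Questions on the use and perceived impact of major modifications, with telehealth as the example, are to go on the quarterly and 6-monthly forms. Month indicators and regional key dates give more than a single before/after contrast. None of this records the mode behind a given rating, and none of it separates detection from occurrence.
- **Hospitalization.** The Background reports "OnTrackNY has demonstrated improvements in symptoms, functioning, hospitalization, and work/school participation". That describes past results. It does not establish that hospitalization is still collected, or that it is recorded independently of clinician contact. Table 2 gives examples only, so hospitalization is not excluded.

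Finally, the Guide also draws on fidelity review and stakeholder input, so one biased outcome would not by itself make telehealth look favourable.

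**Conclusion.** The point holds as a limit on interpretation. Table 2's contrast for suicidality and symptoms coincides with a documented change in how clinicians made contact at many sites (the article does not say all). The described model cannot separate true change from changed detection, and the limitations do not mention it.

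The direction is unknown. The size is the relative detection R, which the article does not give. Over the assumed range of 0.7 to 1.2, the recorded rate is off by −30% to +20%, and it is unbiased only at R = 1. The error probabilities rest on assumed base rates, 1700 and 500 independent observations and no clustering, so they are illustrative. They cover suicidality as a yes/no item; nothing was computed for symptom scores. The conclusion that the contrast is not identified needs none of these assumptions. The remedy is cheap and changes what the study can say about suicidality, so it is worth making.

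**What to change.** 1. In Table 2 and Aim 3, report the pre/post estimates for suicidality and symptoms separately for clinician report and for participant self-report, where self-report carries the item.
2. Name psychiatric hospitalization as a participant outcome beside them, after confirming that it is still collected and how it is recorded.
3. Add a sensitivity analysis that divides the recorded post/pre ratio by R over a range fixed in advance, including equal detection (R = 1) and better detection by telehealth (R above 1). Report the R at which the apparent change disappears, which is the recorded ratio itself.
4. In the Guide, do not describe a fall in clinician-recorded suicidality as favourable unless these analyses agree.
5. Add changed ascertainment to the limitations in the Discussion.

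Optionally, add an item to the quarterly form for the contact mode behind the rating. This is prospective only. The supplement was awarded in 2021, so the item cannot recover 2020 ratings, and comparisons by mode within the later period are confounded by who is seen in person.

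Cost: wording and a few more models on data largely in hand. Self-report is sparser, being 6-monthly, and has its own non-response. Admission practice may also have shifted in the pandemic. No single source settles the question, which is why agreement between them is asked for.
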